## Methods

### Study Design

The program comprises 4 sequential studies (Table 1 and Figure 1): 1 cross-sectional study, 2 prospective cohort studies, and 1 randomized controlled trial (RCT). The target populations are adults with mild-to-moderate major depressive disorder (MDD), generalized anxiety disorder (GAD), or primary insomnia (PI), as well as healthy controls. All studies use a common assessment framework including baseline demographics, clinical characteristics, symptom severity, and electroencephalography (EEG), with follow-up assessments at weeks 1, 2, 4, 6, and 8.

**Table 1. T1:** Study description of the individualized (receptive) music therapy research program.

Study	Description	Translational role
Study 1 (Cross-sectional)	A pilot study (n=20; 5 per group: MDD^a^, GAD^b^, PI^c^, and HC^d^) to characterize clinical features and EEG^e^ patterns across the target disorders and healthy controls. These findings will be benchmarked against prior literature to calibrate study procedures.	Findings will be used to calibrate assessment procedures, verify the feasibility of EEG protocols, and generate preliminary hypotheses regarding disorder-specific neurophysiological signatures to guide the analytical framework of subsequent studies.
Study 2 (Prospective Cohort)	An open-label evaluation (n=80; 20 per group: MDD, GAD, PI, and HC) of the efficacy and safety of 8-week nonindividualized receptive music therapy with concurrent EEG monitoring.	Establishes preliminary efficacy benchmarks and identifies EEG features associated with treatment response. These data serve as the reference standard against which the added benefit of individualization is evaluated in study 3.
Study 3 (Randomized Controlled Trial)	A pilot RCT^f^ (n=300; MDD, GAD, and PI) in which participants are randomized 1:1 to receive either nonindividualized receptive music therapy or IMT^g^ for 8 weeks.	Provides the first direct comparison of individualized versus nonindividualized approaches. Clinical and EEG data from studies 1‐3 are pooled to develop a treatment-response prediction model.

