### Sample Size Calculation

Study 3 is a pilot RCT designed to assess feasibility and to generate preliminary effect estimates to inform a definitive future trial. Accordingly, the sample size is based on precision estimation rather than formal power calculation. The primary outcome is the response rate at 8 weeks, defined as a reduction of 50% or greater from baseline in the disorder-specific symptom severity score. We adopted a minimal clinically important difference–anchored CI approach, setting a 20-percentage-point absolute difference in response rates as the threshold for clinical importance. With 50 participants per arm within each diagnostic group, the expected 1-sided 80% CI half-width for the between-group difference in response rates is approximately 8 to 12 percentage points (derived from a response rate of 70% for the control group and a range of between-group differences from 0% to 30%), thereby permitting precise estimation of feasibility metrics and preliminary efficacy signals to plan the definitive trial.

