#### Primary Outcome Analysis

For the response rate at 8 weeks, between-group comparisons will be conducted using chi-square tests, with results reported as risk difference and risk ratio with corresponding 95% CIs. To accommodate the repeated-measures structure of the data (assessments at baseline and at weeks 1, 2, 4, 6, and 8), linear mixed-effects models for repeated measures (MMRM) will be used for continuous outcomes, with fixed effects for treatment group, time, and their interaction; baseline scores will be included as covariates; and random intercepts for participants will be specified to accommodate within-subject correlation. Because study 3 cannot blind participants and the IMT arm involves additional engagement, 2 prespecified sensitivity analyses will probe the robustness of the primary treatment effect to expectation and attention effects: (1) the MMRM and the response-rate models will be refitted with baseline CEQ scores added as covariates; and (2) the analyses will be repeated with adjustment for the Bang Blinding Index to explore whether the estimated treatment effect is attenuated after accounting for residual unblinding. Concordance between the primary (unadjusted) and these expectancy-adjusted estimates will be interpreted as evidence regarding the extent to which any observed benefit is attributable to personalization of the stimulus rather than to differential expectancy or attention. Time to response or remission will be compared between groups using Kaplan–Meier survival curves and the log-rank test. For study 3, the primary analysis will follow an intention-to-treat principle, including all randomized participants according to their assigned group. A supplementary per-protocol analysis will include only participants who complete at least 80% of scheduled listening sessions (ie, a minimum of 45 of 56 daily sessions).

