#### Heterogeneity of Target Disorders, Subgroup Analyses, and Multiple Comparisons

Recognizing that MDD, GAD, and PI differ in symptom profiles and neurobiological mechanisms, the primary analysis of study 3 will pool all 3 disorders to maximize statistical power, with diagnostic group included as a stratification factor in the randomization and as a covariate in all pooled models. Treatment × diagnosis interaction terms will be included in the mixed-effects models to assess whether treatment effects vary by disorder. If significant heterogeneity is detected, disorder-specific results will be reported separately. The analytic hierarchy is specified a priori as follows. The pooled treatment effect (IMT vs nonindividualized therapy), adjusted for diagnosis, is the confirmatory primary contrast. Disorder-specific treatment effects (MDD, GAD, and PI analyzed separately) are prespecified secondary, hypothesis-generating analyses. For each disorder, we will report the response-rate difference and the MMRM-derived between-group difference in symptom change with 95% confidence intervals, regardless of statistical significance, so that the direction and precision of the per-disorder estimates are transparent and can inform the design of a future definitive trial. The treatment × diagnosis interaction will be evaluated primarily as a test of effect-modification rather than as a gatekeeper for reporting; disorder-specific estimates will be presented whether or not the interaction term reaches significance, but will be explicitly labeled exploratory. We acknowledge that this pilot is not powered for confirmatory subgroup inference. With approximately 50 participants per arm per disorder (100 per diagnostic group), each disorder-specific contrast has limited power to detect between-arm differences smaller than a large effect, and the trial is powered for precision of estimation rather than for hypothesis testing within subgroups (see Sample Size Calculation). To avoid over-interpreting unstable subgroup estimates, the disorder-specific analyses will be supplemented by a hierarchical Bayesian model in which disorder-specific treatment effects are treated as exchangeable and shrunk toward the overall pooled effect; this borrows strength across the 3 disorders and yields more stable, less extreme per-disorder estimates than fully separate analyses. Posterior means and 95% credible intervals for each disorder will be reported alongside the frequentist estimates. We will not draw definitive efficacy conclusions for any individual disorder from study 3; rather, the per-disorder estimates will be used to generate hypotheses and to inform stratified sample-size planning for the definitive trial. It should be noted that the music therapy protocol uses the same affective trajectory for participants with MDD and GAD, whereas a distinct biphasic trajectory is used for participants with PI. This difference in trajectory design reflects the distinct clinical objectives for each disorder and will be accounted for in the analysis by including trajectory type as a covariate in sensitivity analyses. Because trajectory type is collinear with the PI-versus-(MDD and GAD) distinction, this covariate adjustment will be reported as a sensitivity analysis complementary to the disorder-stratified analyses above. For the family of disorder-specific secondary contrasts, the false discovery rate will be controlled using the Benjamini–Hochberg procedure, and both adjusted and unadjusted *P* values will be reported.

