Several limitations should also be noted. First, the open-label design of study 2 precludes causal attribution of observed improvements to the intervention, as natural symptom fluctuation and regression to the mean cannot be excluded in the absence of a control group. However, this limitation is mitigated by the inclusion of a randomized controlled comparison in study 3. Second, complete participant blinding in the RCT is not feasible owing to the inherent differences between the 2 intervention arms, which may introduce differential expectancy effects; moreover, the weekly preference assessment in the IMT arm provides additional participant–researcher contact, engagement, and a sense of agency that is absent from the nonindividualized arm, so that any observed superiority of IMT could in principle reflect this added attention and engagement (a cointervention and attention effect) rather than personalization of the musical stimulus per se. To address these concerns, we have implemented several strategies to minimize bias, as described in the Randomization and Blinding section, including an attention-matched weekly questionnaire in the nonindividualized arm, baseline measurement of treatment credibility and expectancy with expectancy-adjusted sensitivity analyses, and a formal blinding-integrity (bang blinding index) assessment. We nonetheless recognize that these measures reduce, but cannot fully eliminate, the confounding of personalization with attention and expectancy; cleanly separating these components would require designs such as a 3-arm trial incorporating an attention-matched sham-personalization control, which we identify as an important direction for the definitive trial. Third, the pilot RCT is powered for precision of estimation rather than confirmatory hypothesis testing; consequently, the study may be underpowered to detect clinically meaningful differences within individual diagnostic subgroups, and subgroup analyses should be interpreted as exploratory. Because MDD, GAD, and PI differ in symptom profiles, neurobiology, and even in the affective trajectory of the intervention delivered, pooling them maximizes power for the overall comparison but cannot resolve whether the 3 disorders respond differently to IMT; we have therefore prespecified disorder-stratified estimation, a treatment × diagnosis interaction test, and a hierarchical Bayesian model that shrinks per-disorder estimates toward the pooled effect, and we explicitly refrain from drawing disorder-specific efficacy conclusions from this pilot. Definitive, disorder-specific inference will require an adequately powered, stratified trial. Fourth, all studies conclude at 8 weeks, and the durability of treatment effects beyond the intervention period remains unknown. Finally, although EEG offers excellent temporal resolution for capturing dynamic neural responses to music, it provides limited spatial resolution compared with functional MRI, which may constrain the ability to localize treatment-related changes in deep brain structures; in addition, the EEG analyses are exploratory and not powered for confirmatory neurophysiological inference, particularly at the level of individual disorders.

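### The sample-size half-width of 8 to 12 points is not a 1-sided 80% figure, and the 95% intervals to be reported are about 1.5 times wider

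*Protocol article*

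**What the plan says.** The Sample Size Calculation section bases study 3 on precision and not on power. Its inputs are:

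- Group size: "With 50 participants per arm within each diagnostic group".
- Threshold: the authors describe "setting a 20-percentage-point absolute difference in response rates as the threshold for clinical importance".
- Result: "the expected 1-sided 80% CI half-width for the between-group difference in response rates is approximately 8 to 12 percentage points".
- Origin of the result: "derived from a response rate of 70% for the control group and a range of between-group differences from 0% to 30" percent.

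The section concludes that this allows precise estimation.

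The analysis sections work at another level. The Plan for Statistical Analysis makes all tests 2-sided at .05. Primary Outcome Analysis compares response rates "with results reported as risk difference and risk ratio with corresponding 95% CIs". The section on heterogeneity, subgroups and multiple comparisons also promises 95% intervals for each disorder's response-rate difference.

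That section further states: "The pooled treatment effect (IMT vs nonindividualized therapy), adjusted for diagnosis, is the confirmatory primary contrast". It calls the single-disorder estimates exploratory. Strengths and Limitations, however, says that "the pilot RCT is powered for precision of estimation rather than confirmatory hypothesis testing".

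**The concern.** The half-width is the only quantitative support for 300 participants, and the pilot is meant to inform a definitive trial. All of its inputs are printed, so it should reproduce, and under its label it does not.

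Three further points affect how the number will be read:

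- It is set at an 80% level, while every interval the trial will publish is at 95%. A reader who compares 8 to 12 points with the 20-point threshold will expect tighter single-disorder results than the trial can give.
- The favourable end of the range comes from an extreme scenario.
- The figure describes the single-disorder contrasts, which the plan treats as exploratory. The pooled contrast, which it calls confirmatory, has no figure at all.

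**Working it through.** **Inputs.** From Sample Size Calculation: n = 50 per arm per disorder, control response pc = 0.70, IMT response pt = 0.70 to 1.00 (differences 0 to 30 points). From Study Design: "participants are randomized 1:1 to receive either nonindividualized receptive music therapy or IMT". Three disorders therefore give 3 × 50 = 150 per arm pooled.

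**Formula.** Half-width = z × SE, with SE = √[pc(1−pc)/n + pt(1−pt)/n].

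- Difference 0: SE = √(0.21/50 + 0.21/50) = 0.0917.
- Difference 10: SE = √(0.21/50 + 0.16/50) = 0.0860.
- Difference 20: SE = √(0.21/50 + 0.09/50) = 0.0775.
- Difference 30: SE = √(0.21/50 + 0) = 0.0648.

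**Reproducing the stated figure (50 per arm, percentage points).**

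| Level | z | diff 0 | diff 10 | diff 20 | diff 30 |
|---|---|---|---|---|---|
| 1-sided 80% (as labelled) | 0.842 | 7.7 | 7.2 | 6.5 | 5.5 |
| 2-sided 80% = 1-sided 90% | 1.282 | 11.7 | 11.0 | 9.9 | 8.3 |
| 2-sided 95% (as reported) | 1.960 | 18.0 | 16.9 | 15.2 | 12.7 |

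The second row rounds to the printed 12 and 8 at its two ends; the first row does not. Working backwards, 0.12/0.0917 gives z = 1.31 and 0.08/0.0648 gives z = 1.23. These are 1-sided confidence levels of about 90% and 89%.

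**Other routes to 8 to 12 at 1-sided 80%.** None works:

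- pooled variance: 7.7 to 6.0
- Newcombe-Wilson: 7.7 to 5.5
- Agresti-Caffo: 7.6 to 5.6
- continuity correction (adding 1/n): 9.7 to 7.5
- differences in the negative direction: about 8.0 to 8.1 (10.0 to 10.1 with the correction)
- an assumed 20% loss (n = 40): 8.6 to 6.1 (11.1 to 8.6 with the correction)

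**The 8-point end.** A 30-point gain on 70% is 100% response on IMT. That arm then adds nothing to the variance, which is why the interval looks narrow.

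**Direction of the error.** Under the label as printed, n = [0.21 + pt(1−pt)] × 0.842² / (half-width)². A half-width of 12 at difference 0 needs about 21 per arm. A half-width of 8 at difference 30 needs about 24. Fifty per arm more than meets the printed criterion.

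**Reported level, per disorder.** The 95% half-width is 1.960/1.282 = 1.53 times the planning figure. An observed difference of 0 gives about −18 to +18. An observed difference of 20 gives 20 ± 15.2, about 5 to 35.

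**Pooled contrast (150 per arm).** The 95% half-widths are 10.4, 9.7 and 8.8 points at differences of 0, 10 and 20. Exact binomial power of the 2-sided .05 chi-square test, from 70% control:

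| Difference | Uncorrected | Continuity-corrected |
|---|---|---|
| 10 points | 52% | 46% |
| 15 points | 88% | 85% |
| 20 points | 99% | 99% |

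Descriptive and Baseline Analyses prescribes the correction for 2×2 tables; Primary Outcome Analysis does not say whether it applies. Neither column includes the adjustment for diagnosis.

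**The case against.** The best defence is that the slip is harmless. A true 1-sided 80% limit is closer to the estimate than the text claims, so the printed label makes the trial look less precise than it is at that level. The sample size, arms and analyses are unaffected. This stands, and it limits the severity.

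Nor does planning at 80% while reporting at 95% contradict anything in itself. The section states its level, the pilot purpose and the absence of a power calculation. That also stands; what is missing is a sentence telling the reader how wide the published intervals will be.

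The plan is also candid about single disorders. It concedes limited power for anything below a large effect, labels those results exploratory and adds a shrinkage model. This weakens any charge of concealment, but it also shows that the claim of precise estimation does not fit the per-disorder figure it is attached to.

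A reader might infer that 50 per arm fails the 20-point criterion once 95% intervals are used. The documents do not support that: at an observed difference of 0 the 95% limit is 18.0 points, which still excludes 20.

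A reader might also take it as settled that 2-sided 80% was meant. One-sided 90% gives identical numbers, so the text cannot show whether the sidedness or the level is wrong.

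**Conclusion.** The stated half-width is wrong as labelled: 7.7 to 5.5 points at 1-sided 80%, against a printed 8 to 12 that matches z = 1.282. The 95% half-widths per disorder are about 15 to 18 points for differences of 0 to 20, roughly 1.5 times the printed range. These are half-widths; the full intervals span about twice as much.

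The missing pooled figure and the inconsistent use of confirmatory language are real but secondary. It would be tempting to conclude that the trial is too small. That does not follow: the printed criterion is met, and the pooled half-width is about 9 to 10 points over the same differences.

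The results rest on the 70% control rate, full follow-up of 50 per arm and the unpooled normal approximation. Newcombe-Wilson half-widths at 95% are close (17.5 at difference 0, 15.3 at 20). Losses would widen all of them; the article gives no dropout rate. Severity: should be fixed.

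**What to change.** In Sample Size Calculation:

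1. Correct the label, with the sponsor stating whether 2-sided 80% or 1-sided 90% was intended. Or keep 1-sided 80% and correct the number.
2. Add the 2-sided 95% half-widths for differences of 0 to 20 points: about 15 to 18 per disorder and about 9 to 10 for the pooled contrast at 150 per arm.
3. Drop the 30-point scenario, which implies 100% response.
4. Confine the claim of precise estimation to the pooled contrast, in keeping with the exploratory status of the single disorders.

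Then make Sample Size Calculation, the heterogeneity and subgroup section, and Strengths and Limitations agree on whether the pooled contrast is confirmatory. If power is quoted for it, name the test and say whether the continuity correction applies.

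The cost is wording only. No participants are added, but the stated per-disorder precision becomes less favourable.

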### Randomization and Blinding

For the RCT, an independent biostatistician will generate the allocation sequence using SAS software (version 9.4; SAS Institute). Randomization will be managed via a secure, web-based system to ensure allocation concealment. Upon confirmation of eligibility and completion of baseline assessments, the system will release the assignment to a research nurse who is not involved in outcome assessment. Outcome assessors will remain blinded to group assignment throughout the trial. Given the nature of the intervention, complete participant blinding is not feasible, as those in the IMT arm engage in weekly preference assessments and music selection, whereas participants in the nonindividualized arm receive therapist-curated tracks without weekly customization. Beyond the impossibility of participant blinding, we explicitly recognize that the weekly preference assessment and track-rating procedure in the IMT arm constitutes an additional, potentially active, component of participant–researcher interaction and engagement that is not present in a conventional nonindividualized protocol. Any between-arm difference in outcomes could therefore reflect not only the personalization of the musical stimulus itself but also this greater attention, engagement, and sense of agency. To mitigate both expectation bias and this attention and engagement confound, several strategies are used: (1) participants in both arms are informed only that they will receive music therapy, without being told which approach is hypothesized to be superior; (2) all participants complete equivalent contact time and daily listening schedules; specifically, participants in the nonindividualized arm complete a weekly music-experience questionnaire covering their listening experience, mood, and engagement, that is matched to the IMT arm’s weekly preference assessment in length, frequency, mode of administration, and degree of staff contact, so that the 2 arms are equated for attention and procedural engagement and differ only in whether the questionnaire responses are used to regenerate the following week’s music; and (3) primary outcomes are assessed by independent raters who have no knowledge of treatment allocation. In addition, to render expectation effects measurable rather than merely assumed, all participants complete a validated treatment-credibility and outcome-expectancy measure (the Credibility/Expectancy Questionnaire, CEQ) after allocation and before the first session; baseline expectancy scores will be compared between arms and entered as a covariate in prespecified sensitivity analyses of the primary outcomes. To assess the integrity of assessor blinding and to characterize residual participant unblinding, both participants and outcome assessors will be asked to guess the participant’s allocation at week 8, and a blinding index (bang blinding index) will be computed and reported. Unblinding of assessors is permitted only in the event of a medical emergency.

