#### IMT

IMT uses an artificial intelligence (AI)–enabled pipeline to tailor the interventions to weekly patient preferences. Before each week’s session, participants complete a preference questionnaire across 6 dimensions: emotion, style, intensity, instrumentation, variation, and tempo. These inputs are converted into standardized prompts for the Suno music platform (V4 model; API: sunoapi.org). For example, a selection of “calm, Western Classical, flute and piano and cello, slow tempo” is programmatically rendered into a specific generation prompt. The system generates 16 unique instrumental tracks, which the participant rates on a 1‐7 scale. The 8 highest-rated tracks are compiled into the 30-minute intervention set for that week. To ensure therapeutic consistency across participants, the AI-generated tracks are subject to predefined acoustic constraints. All generated tracks are required to be purely instrumental (lyrical content is excluded). Furthermore, key acoustic features, including tempo (beats per minute), spectral centroid, and rhythmic complexity, are logged for each generated track. The therapeutic structure of the IMT condition mirrors that of the nonindividualized arm in session duration (30 min daily), number of tracks per session (6 to 10 excerpts), and overall affective trajectory framework. The sole difference lies in the source of the musical material (AI-generated based on individual preferences vs therapist-curated from existing libraries). Participants are instructed to listen once daily in a quiet environment and to focus their attention on the auditory experience and the emotions it evokes. The playback interface displays the following guidance: “Please adjust your posture to feel relaxed and comfortable. Close your eyes and begin deep breathing. After the music begins, focus all your attention on the music and the feelings it evokes.”

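### Agreement between unadjusted and expectancy-adjusted estimates cannot tell personalization from attention, and the two arms differ in more than the use made of the weekly questionnaire

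*Protocol article*

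**What the plan says.** **Matching of arms.** Randomization and Blinding first describes IMT's preference assessment and its track rating as an extra and possibly active element. It then introduces a weekly control questionnaire, matched to the preference assessment, and concludes: "2 arms are equated for attention and procedural engagement and differ only in whether the questionnaire responses are used to regenerate the following" (that is, the next set of tracks).

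**What IMT participants do.** The IMT section has them complete a six-dimension preference questionnaire each week. Then: "The system generates 16 unique instrumental tracks, which the participant rates" from 1 to 7. "The 8 highest-rated tracks are compiled into the 30-minute intervention set for that week".

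**What controls do.** According to Randomization and Blinding and the Nonindividualized Receptive Music Therapy section, their questionnaire asks about listening, mood and engagement, and the answers leave the track list as it was.

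**Adjusters.** The CEQ is completed "after allocation and before the first session; baseline expectancy scores will be compared between arms and entered as a covariate" in sensitivity analyses. At week 8, participants and assessors guess the participant's "allocation at week 8, and a blinding index (bang blinding index) will be computed and reported".

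**Interpretation.** Primary Outcome Analysis refits the models with CEQ scores, and separately "the analyses will be repeated with adjustment for the Bang Blinding Index". Concordance with the unadjusted result is to be taken as evidence on how far any benefit is "attributable to personalization of the stimulus rather than to differential expectancy or attention".

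**Stated limits.** Strengths and Limitations says IMT's weekly assessment brings contact, "engagement, and a sense of agency that is absent from the nonindividualized arm". It lists the mitigations and accepts that they lessen the confounding without removing it. Future Directions leaves a sham-personalization arm to the definitive trial.

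**The concern.** A sensitivity analysis can speak only to the influences that its covariates measure. Here the conclusion names two rival explanations, expectancy and attention, but the covariates concern expectancy and beliefs about allocation. Suppose part of an IMT benefit came from auditioning, rating and choosing music, or from the engagement that goes with it. The CEQ-adjusted estimate could then agree closely with the unadjusted one, and the prespecified reading would count that agreement in favor of personalization.

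The statement about the arms makes this reading look safer than it is. If the arms truly differed only in whether answers regenerate the music, there would be little attention difference left to worry about. The IMT procedure as described does not fit that.

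At stake is the explanation attached to the primary result. It matters because the program's argument is that the musical stimulus itself is what is being improved.

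**Working it through.** The plan states no figure on this point, so there is none to reproduce. The check is a comparison of the text, a short algebraic argument and two counts.

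**1. What the described arms contain**

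| Weekly element | IMT | Nonindividualized |
|---|---|---|
| Questionnaire | preference, six dimensions | listening experience, mood, engagement |
| Candidate tracks rated | 16 | none described |
| Own ratings select the music | yes, 8 of 16 | none described |
| Music renewed from responses | yes | no |

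Over 8 weeks this is 16 × 8 = 128 ratings and 8 × 8 = 64 selected tracks per IMT participant. Time spent auditioning is not given, so no minutes are claimed. The claimed single difference covers only the last row.

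**2. What the adjusters measure**

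- CEQ: credibility and expectancy, once, before the first session. It does not measure attention, agency or the rating task.
- Bang index: how far allocation guesses at week 8 depart from chance. It does not measure attention either.

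**3. What concordance can show**

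Let T be arm (1 = IMT), E the CEQ score, p the effect of personalized music and r the effect of rating, selection and attention. Take a linear outcome model:

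Y = a + (p + r)T + gE + error

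Let δ be the difference between arms in mean CEQ. Then:

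- unadjusted arm effect = p + r + gδ
- CEQ-adjusted arm effect = p + r
- gap between them = gδ

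The gap depends on expectancy alone. The split between p and r appears nowhere, because both are carried by the same arm indicator.

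As an illustration with assumed values (SD units), take p + r = 0.4, g = 0.3 and δ = 0.3. The unadjusted effect is 0.4 + 0.3 × 0.3 = 0.49, the adjusted effect is 0.40 and the gap is 0.09. With p = 0.4 and r = 0, or with p = 0 and r = 0.4, all three numbers are identical. With δ = 0 the estimates agree at 0.40 in both cases. The same holds for a response-rate model, since the data again depend on p and r only through their combined effect.

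**4. Whether the Bang adjustment helps**

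The index is a summary computed for each arm. Write its value as b₁ in IMT and b₀ in control. As a covariate it equals b₀ + (b₁ − b₀)T, an exact linear function of the intercept and arm. The three columns (intercept, arm, index) have rank 2, so the adjusted arm effect cannot be estimated. Individual guesses avoid the collinearity. But they are collected at the outcome visit, so improvement may shape the guess, and they still measure belief about allocation.

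**The case against.** The strongest reply is that the authors already say most of this. Randomization and Blinding admits that attention, engagement and agency could explain a difference, and Strengths and Limitations and Future Directions name the design that would separate them. A reader might infer that the confound is hidden; it is not. That disclosure stands, but a limitation in the Discussion does not correct an interpretation prespecified in the Methods.

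Second, the concordance sentence sets no threshold and triggers no decision. That is so. It is an interpretive statement, and the objection here is only to its including attention.

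Third, the preference assessment might be shorthand that includes track rating, with the detail left to a fuller protocol. Randomization and Blinding, however, names track rating separately and matches the control questionnaire only to the preference assessment. Even with time matched, reporting mood is a different task from choosing one's own music.

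Fourth, a reader might take "engagement, and a sense of agency that is absent from the nonindividualized arm" as a flat contradiction of the claim that the arms are equated. In context it states the worry before the mitigations are listed. The usable point is narrower: claiming the arms are equated is stronger than conceding that confounding remains.

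Fifth, the IMT section's remark that only the source of the music differs might look false. It follows a sentence on session length, track count and trajectory, so it reads as describing the delivered session and is not part of this point.

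Last, the order of the CEQ and the first week's rating is not stated, so some rating might precede the CEQ. That would not make the CEQ a measure of attention over 8 weeks.

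**Conclusion.** The point holds in a limited form. Concordance with the CEQ-adjusted estimate can inform on baseline expectancy. It cannot inform on attention, and it cannot by itself establish personalization as the cause. The Bang-adjusted analysis adds nothing on either question, and with one index value per arm it cannot be fitted. The claim that the arms are equated and differ in one respect is too absolute, given a weekly rating and selection step described for IMT alone.

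A reader might infer that the primary comparison is biased or invalid. The documents do not support that. The confirmatory contrast in the section on heterogeneity of target disorders is IMT against nonindividualized therapy, a comparison of whole packages, and it keeps its meaning whichever component is active. Only the mechanistic reading is affected. The size and direction of any attention or rating effect are not given and are not estimated here.

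The conclusion rests on the control procedure being as described in the article, and on the CEQ and the Bang index being the only adjusters tied to the concordance statement. It should be corrected before the analysis plan is finalized.

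**What to change.** **Primary Outcome Analysis**

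- Delete *or attention* from the concordance statement.
- Limit concordance with the CEQ-adjusted estimate to a statement about baseline expectancy.
- Report the Bang index descriptively by arm, and draw no inference about attention or personalization from a Bang-adjusted analysis.
- Attribute any between-arm effect to the IMT package: preference-based generation, track rating and selection, and weekly renewal.

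**Randomization and Blinding**

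Replace the claim of equated arms with wording such as: *the questionnaires are matched in length, frequency, mode and staff contact; the arms still differ in track rating, selection and weekly renewal.*

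**Cost**

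These are text changes. The confirmatory contrast, the sample size and the primary estimate stay as they are, and the CEQ-adjusted analysis is kept. The authors give up a mechanistic statement that the data cannot support and that their own limitations section already qualifies.
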